## Abstract

**Introduction:**

Depression is a common psychiatric disorder characterized by persistent low mood, reduced interest, and slowed thinking. Young adults are the main first-onset group for depression in all categories of the population. Program for education and enrichment of relational skills (PEERS) training, a program for the Education and Enrichment of Relational Skills, has been used in Europe and America for people with various types of social disorders with good results. A Chinese adaptation of the PEERS training program may be a new approach to help youth with depression return to society as soon as possible. This study aimed to construct and optimize a social skills training program for Chinese young adults with depression and to validate the impact of the program.

**Materials and methods and analysis:**

The aim of this trial protocol is to evaluate the efficacy of the localized PEERS training program on social competence, depressed mood in a Chinese young adult population with depression. The primary outcome will be a change in self-reported depressive symptoms from baseline to week 3 post-randomization to week 6 post-randomization measured using the Liebowitz social anxiety scale (LSAS). Secondary outcomes include the rate of decline in severe social anxiety, the Social Avoidance and Distress Scale (SAD), the Social Self-Efficacy Scale (PSSE), and the Hamilton Depression Scale (HAMD-17). Data for each assessment will be collected at baseline, week 3 of the trial, and week 6 of the trial.

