### Outcome measure

The measurement of each scale measure, the outcome indicators will all be carried out by investigators who are not involved in the implementation of the intervention.

A baseline survey will be conducted by the investigator after the study subjects are identified, and basic information will be collected on the subjects, including age, gender, marital status, mode of payment (self-pay, agricultural insurance, medical insurance, and others), type of depression (general depressive disorder, anxiety depressive disorder, and others), previous history, family history, duration of illness and medication use, etc.

Considering that the first onset of action of antidepressants is between 2 and 4°weeks (46), We, therefore, chose to collect the subjects’ depression scores at three-time points: baseline, week 3 of the intervention and week 6 of the intervention. The scales were selected based on clinical applicability and reliability to dynamically assess the efficacy of the localized PEERS training.

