### Primary outcome

Liebowitz social anxiety (LSAS) at week 3 and week 6 of the intervention will be assessed to measure social anxiety.

The LSAS scale was developed by Liebowitz in 1987 (47). It is commonly used to assess subjects’ social anxiety and is one of the most commonly used scales to provide a good picture of a subject’s social situation. The 24-item scale assesses fear in 11 social and 13 operational contexts. Scored on a four-point scale, for the fear subscale: 0 (none); 1 (mild), tolerable; 2 (moderate), distressing; 3 (severe), seriously interferes with daily life and work. For the avoidance subscale: 0 (never), 1 (occasionally), 2 (often), 3 (always). The final scores are added together, and the higher the total score, the more severe the social anxiety state. Mild anxiety is defined as a total score of less than 16, while severe anxiety is defined as a score of more than 60 (48). The Chinese version of the LSAS was tested for reliability and validity, and the Correlation between the items and the total score was good, the Cronbach’s α coefficient of each subscale was greater than 0.9, and the total scale score of the retest reliability was 0.779, the scale was generally satisfactory (49).

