#### Official experiment

This trial is a clinical intervention study, and the primary outcome indicator is the LSAS score. Compare sample size formulae based on means $n=\frac{2^{2}\,{\left(\mu_{\alpha }+\mu_{\beta }\right)}^{2}\,\sigma^{2}}{\delta^{2}}$. Take α = 0.05, β = 0.10. From the pre-test, we can calculate that σ2 = 243.04 and δ2 = 272.25, estimating a sample size of about 62 cases, and considering a 20% missed visit, 62 + 62*0.2 = 74, 74 patients are to be included in the formal trial, 37 in the intervention group and 37 in the control group.

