### Statistical methods

For baseline comparisons, age, LSAS scores, SAD scores, PSSE scores, and total HAMD-17 scores are measurement data for both two groups and will be statistically described using the mean ± S.D., with Paired Sample *T*-Test used to assess between-group balance. The general profile of the test subjects, including gender, education level, occupation, marital status, mode of payment for medical care, per capita household income, type of depression, duration of illness, type of medication, family history, and past history, are all categorical data that will be statistically described using frequencies and percentages, and chi-square tests to assess between-group balance.

The primary outcome indicators (LSAS scores at week 3 and week 6 post-intervention for two groups of patients) and secondary outcome indicators (SAD, PSSE, HAMD-17 scores at week 3 and week 6 post-intervention for two groups of patients) will be compared using Repeated Measures ANOVA to analyze the efficacy of PEERS training at different time periods. Considering the possible interaction between intervention and time, we choose Simple Effects to analyze the different effects of different time variances on PEERS training.

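### The abstract labels the primary outcome as depressive symptoms although its scale measures social anxiety, and the plan names no primary visit, clock or deciding between-arm test

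*Protocol article*

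**What the plan says.** The protocol article describes the primary outcome in four places.

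- **Abstract (Materials and methods and analysis):** "The primary outcome will be a change in self-reported depressive symptoms from baseline to week 3" and on to week 6, counted from randomization and "measured using the Liebowitz social anxiety scale (LSAS"). HAMD-17 is listed among the secondary outcomes.
- **Primary outcome:** "Liebowitz social anxiety (LSAS) at week 3 and week 6 of the intervention will be assessed to measure social anxiety".
- **Sample size, Official experiment:** "the primary outcome indicator is the LSAS score", with no visit named.
- **Statistical methods:** "The primary outcome indicators (LSAS scores at week 3 and week 6 post-intervention for two groups of patients"), in the plural. These, like the secondary scales, "will be compared using Repeated Measures ANOVA to analyze the efficacy of PEERS training at different time periods". Simple effects are added because intervention and time may interact.

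Three other sections bear on this. Outcome measure explains the visit schedule by saying that the authors "chose to collect the subjects’ depression scores at three-time points". Secondary outcome lists HAMD-17 as the depression scale. Statistical data collection says a psychologist administers HAMD-17, and gives P < 0.05 as the only significance rule.

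**The concern.** A primary outcome should fix what is measured, in what form, when, and by which comparison. Here the abstract names one construct and an instrument for another. The abstract uses change and the body uses scores. Two visits share primary status, and the ANOVA produces several effects without saying which one answers the question.

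At stake is what may be reported as the trial's main result. As written, an LSAS finding could be described as an effect on depressive symptoms. The authors could also choose between week 3, week 6 and an overall ANOVA effect after seeing the data.

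**Working it through.** **1. Construct.** The abstract pairs depressive symptoms with the LSAS, and the Primary outcome section says the LSAS measures social anxiety. The only depression scale is HAMD-17, which is secondary and administered by a psychologist, so it is not self-reported. No listed instrument measures self-reported depressive symptoms, and the abstract's definition cannot be carried out as worded. The rationale in Outcome measure repeats the slip for the whole visit schedule.

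**2. Form.** The abstract says change from baseline; Primary outcome, Official experiment and Statistical methods refer to the LSAS or LSAS scores. The sample size does not settle which was meant:

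- The stated δ² = 272.25 gives δ = 16.5.
- The Table 3 difference in final LSAS score is 51.50 − 41.75 = 9.75.
- The Table 3 difference in LSAS change is (55.50 − 41.75) − (52.25 − 51.50) = 13.00.

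The planning difference matches neither. The stated 62 is not reproduced either: 4 × (1.960 + 1.282)² × 243.04 / 272.25 = 37.5 in total for two-sided α = 0.05 and 90% power. That mismatch is a separate matter, and nothing below depends on it.

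**3. Clock.** The abstract counts weeks after randomization, Primary outcome counts weeks of the intervention, and Statistical methods counts weeks after it. Under Assignment of intervention, wards are randomized before eligible patients are sought in them, so weeks since randomization need not equal weeks since a patient began. Read literally, six weeks after the intervention falls beyond the end of the six-week course.

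**4. Deciding test.** A repeated measures ANOVA gives group, time and group-by-time effects, and simple effects add comparisons at each visit or within each arm. The protocol does not say whether baseline is a level of the time factor, which changes what the interaction means:

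- With baseline included, group by time tests whether the arms change differently.
- With weeks 3 and 6 only, it tests whether the arm difference alters between those visits. An equal benefit at both would appear in the group effect, not in the interaction.

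**5. Two visits, under an assumed rule.** Suppose that a significant arm difference at either visit, at two-sided 0.05, counts as success. With no true effect and correlation r between the two test statistics:

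P(at least one significant) = 1 − P(|Z₁| < 1.96 and |Z₂| < 1.96)

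| r (assumed) | False-positive risk |
|---|---|
| 0 | 1 − 0.95² = 9.75% |
| 0.5 | 9.1% |
| 0.7 | 8.3% |
| 0.8 | 7.8% |

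The document gives no correlation between weeks 3 and 6. The LSAS retest reliability of 0.779, quoted under Primary outcome, would give 7.9% if used as a stand-in. The figures ignore the allocation by ward.

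**The case against.** The best defence is that the instrument never varies. Wherever status is given, the LSAS is primary and HAMD-17 secondary, so the abstract most likely contains a mislabel. This stands. A reader might infer that depression, or HAMD-17, could be declared primary. The text does not support that: the abstract itself names the LSAS and says self-reported, which excludes HAMD-17.

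Second, the visits are analysed together in one ANOVA, and nothing says that either visit alone means success. This also stands, so the error rates in the table are conditional and are not a property of the plan. It does not clear the plan, because no single test is committed to and simple effects follow.

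Third, score and change may be reconcilable. If baseline is a level of the model, group by time on scores tests differential change. The gap between 13.00 and 9.75 is exactly the pilot's baseline imbalance, 55.50 − 52.25 = 3.25, with six patients per arm. It says nothing about how far the choice would move the main trial's result.

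Fourth, a reader might infer that a time effect or a within-arm improvement would be taken as efficacy. No section says so, and Statistical methods speaks of comparing two groups.

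Finally, an article may leave the choice of ANOVA term to a fuller document. On its own that would be a fair reply. It does not cover a printed contradiction in the construct, or two visits explicitly given joint primary status.

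**Conclusion.** The point holds as an inconsistency in the printed definition of the primary outcome, together with two unranked primary visits, three descriptions of the clock and no named deciding between-arm contrast. The construct error is certain from the text. The statistical cost depends on how the result would be declared: about 9.1% to 7.8% in place of 5% if either visit could count unadjusted, at assumed correlations of 0.5 to 0.8, and no inflation from the two visits if one group-by-time test were fixed in advance. It should be settled before outcomes are seen by arm, because it determines what the trial's main result is.

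**What to change.** - **Abstract:** name social anxiety, not depressive symptoms, as the primary construct.
- **Outcome measure:** refer to scale scores rather than depression scores when explaining the three visits.
- **Abstract, Primary outcome, Statistical methods:** use one clock, weeks from the start of the intervention. State which date stands in for control patients, who start no course; the baseline assessment is one option.
- **Primary outcome, Official experiment, Statistical methods:** state one primary test in the same terms, for example the between-arm difference in LSAS total at week 6 adjusted for baseline LSAS. Make week 3 LSAS and HAMD-17 secondary.
- **Alternatives that would also serve:** one prespecified group-by-time test, stating whether baseline is a level of time; or both visits kept primary at 0.025 each, which holds the overall risk to at most 0.025 + 0.025 = 0.05.
- **Interpretation:** add a sentence saying that efficacy rests on that between-arm contrast and not on time or within-arm effects.

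The change is to wording only. Under the week 6 option, the downside is that week 3 can no longer carry a primary claim.

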**Ethics and dissemination:**

Ethics approval was obtained from the Hospital Ethics Committee. Findings will be disseminated through scientific journals, conferences, and university courses.

**Trial registration number:**

[http://www.chictr.org.cn/], identifier [ChiCTR2100046050].

## Introduction

Around the world, depression is one of the most common mental health problems and is ranked by the WHO as the single largest contributor to global functional disability (1). In fact, mental disorders account for 30% of the non-fatal disease burden worldwide and 10% of the overall disease burden, including death and disability (2). The total number of people living with depression worldwide in 2015 was estimated to be 322 million, or 4.4% of the total population. Nearly half of these people live in the South-East Asia Region, and Western Pacific Region (1), which include India and China, for example.

The prevalence of depression affects different age groups, and in various analyses of depression in youth, it was found that the prevalence of depression in young students was about 27.2% (3), about 5% of people aged 65 and over suffered from depression (4). In the first-episode group, there is a predominance of young adult (5). Youth morbidity can have a serious impact across the life cycle (6); the earlier the age of onset, the higher the risk of obsessive-compulsive, interpersonal sensitivity, depression, hostility, paranoid ideation, and psychoticism, the more pronounced the clinical features and the higher the degree of impaired social function (7). Early and effective intervention is therefore needed.

Research shows that people with depression experience impaired social functioning (6–9), even up to 20% of depressed people have severe social anxiety (9). The study finds depression with social anxiety associated with worsening depression (8, 10–12), cases with impaired social function have more physical symptoms, more residual symptoms of depression, and less satisfaction with the quality of life (13). After depressed disease are prone to heavy psychological burden and anxiety, fear and other negative emotions, but individual in society, the essential need to mix with all sorts of people, because of interpersonal communication is impaired, patients unable to integrate into the collective and society, unable to perform normal in daily work, and then form a vicious circle (14). While interpersonal harmony and emotional stability play complementary roles, social training can reduce social anxiety and reduce depressive symptoms. A study of prenatal depression patients who received 12-week social support training showed that attending a social support group reduced depression and social anxiety and improved intimacy (15). Through the vulnerability model of social skills deficit (16), Moeller RW verified that the low level of social skills of college students is correlated with the high rate of loneliness. The development of social skills programs can reduce the loneliness of college students with depression and anxiety, and further reduce their mental health burden (17). Early social skills training can be effective in reducing social anxiety and depression (18–20).

Clinical social skills training include interpersonal therapy (IPT) (21), social skills training (SST) (22), dynamic interpersonal therapy (DIT) (23), and so on. IPT is currently the mainstay of treatment for social dysfunction in patients with depression. It was originally developed by Gerald Klerman and Myrna Weissman as a psychological treatment for outpatients with severe depression (24), based on “psychobiological approach” of Adolf Meyers (25), “Interpersonal School” of Harry Stack Sullivans (26) and “Attachment theory” of John Bowlbys (27). Numerous clinical randomized controlled trials have confirmed the effectiveness of IPT in the treatment of patients with depression (28). But for now, IPT is more focused on patients with postpartum depression (21) and helping new mothers adjust to the role change. SST refers to helping patients simulate normal communication and communication methods by teaching patients’ social communication skills, so as to stimulate patients to find the joy of life and play a therapeutic purpose (22). The training includes four main areas: language skills, basic interpersonal skills, self-confidence, and skills in helping others and seeking help. DIT is based on building alliances of help and trust, and emphasizes the connection between this alliance and the patient’s past experiences (29). Take the lead of the therapist to help the patient relax and communicate effectively while dealing with interpersonal challenges (30). These social skills training exercises have been shown to be effective in guiding social function in people with depression, but they are mainly aimed at people of all ages with depression. The vast majority of evidence focuses only on depression itself, ignoring the differences in the context of the family environment at different ages, taking into account the age-specific nature of the youth population, which differs from adults and older people in the way they approach relationships (31). All of these training lack relevance to the youth depression population, and there is an urgent clinical need for a social intervention for a young adult with depression.

Program for Education and Enrichment of Relational Skills (PEERS) is a training program developed by [name] at UCLA (University of California, Los Angeles, Los Angeles, CA, United States) to address social skills deficits (32–34). It is a parent-assisted, manualized social skills training program for adolescents with ASD. PEERS training focus on key areas of social function for young people, including such as developing conversational skills, choosing appropriate friends, using humor, planning get-togethers, using good sportsmanship, and handling peer rejection, such as teasing physical bullying, gossiping, and disagreements. Teaching ecologically effective skills to nurture and maintain friendships using psycho-educational and cognitive-behavioral therapy techniques (35). PEERS training has been successively introduced and updated locally in Korea (36), Japan (37), Israel (38), the Netherlands (39), and Hong Kong (40), with good results in local ASD patients (41). Patients with ASD are often accompanied by depression, anxiety, intellectual disability, attention deficit, and other psychiatric comorbidities. The results of the study showed that after the PEERS intervention, patients’ social etiquette and social functioning scores improved significantly, their social communication skills, responsive and accepting behavior improved positively, and depressive symptoms were effectively reduced (40).

Since the development of PEERS training, a number of researchers have used various trials to evaluate the effect of PEERS training on the mental health of patients (42). It has been suggested that the PEERS program could help more people with impaired social functioning to exercise their social functions (40), such as people with depression. In North America, the PEERS training has been shown to be effective in reducing patients’ self-reported depressive symptoms (32) and has also been extended to patients with depression, anxiety, alcohol dependence, and other disorders (43, 44). This shows that PEERS training has a bright future as an intervention to improve social functioning, similar to IPT, SST, and DIT.

Considering the different cultural backgrounds, social civilizations, and interpersonal styles in mainland China, the applicability of the PEERS training to young Chinese patients with depression still needs to be further optimized and validated. Combining PEERS with the Chinese context and exploring the construction of a more suitable social training program for Chinese young people with depression has positive clinical implications for the new development of psychiatric treatment in China. Influenced by local, regional differences, this trial also provides a reference for the introduction of a locally adapted PEERS training program for depressed youth in countries around the world, contributing to the global spread of PEERS training programs.

### Objective

The aim of this protocol is to localize the PEERS training program in China, validate the efficacy of the Chinese PEERS training on social competence and depression in Chinese youth with depression, evaluate its effectiveness and safety during implementation so that it can better guide the establishment of clinical programs, provide evidence for the choice of new interventions. PEERS is a promising social intervention program that may be a useful addition to existing social intervention programs. The study will provide a reference for the introduction of locally adapted and targeted PEERS training, and promote the application of PEERS training program worldwide.

## Materials and methods and analysis

### Study design

This study protocol conforms to the Standard Protocol Items: Recommendations for Interventional Trials (SPIRIT) guidelines (see Additional file 1) and accords with the SPIRIT Figure (Figure 1). The proposed PEERS training for the trial is based on literature research and expert discussion and is an optimized update of the original PEERS training program. Participant engagement in the trial will be divided into two phases, a non-intervention phase before randomization and an intervention phase 6 weeks after randomization. This trial was designed to validate the efficacy of the localized PEERS training, and therefore the control group in this trial will not receive any interventions other than usual care. Participants will be randomized by ward to receive the intervention, and due to the specific nature of the intervention, blinding will not apply to the interventionists, and the study will remain blind to scale assessors and data entry only.

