### Participants

Trial participants were recruited from young adults with depression attending a specialist mental health hospital in Huzhou from July 2022 to January 2023. It is the largest specialist mental health hospital in the region, with psychological and psychiatric disorders diagnosis and treatment as its specialty, treating people with all types of psychosomatic disorders, with a wide range of influences and strong representation.

The purpose, procedures, possible risks, benefits, and other information about this trial will be explained in detail to participants. The trial participant schedule is specified in Figure 2.

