### Assignment of intervention

Prior to the start of the intervention, different ward were randomly divided into intervention and control groups using a coin toss by an investigator not involved in the implementation of the intervention to prevent contamination, and eligible subjects were sought within the respective ward.

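### Wards are randomised, but the sample size and the repeated-measures ANOVA treat patients as independent: the 5% test is anti-conservative and the 90% power is unsupported

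*Protocol article*

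**What the plan says.** The ward is the unit of allocation in two places. Study design states: "Participants will be randomized by ward to receive the intervention". The section on assignment describes the method: "different ward were randomly divided into intervention and control groups using a coin toss". Recruitment follows that step: "eligible subjects were sought within the respective ward". All wards belong to one hospital (Participants). The article does not say how many wards it contributes.

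The Official experiment subsection sizes the trial with a formula for two means ("Compare sample size formulae based on means"), a variance of 243.04 and a squared difference of 272.25. The error rates are given as "Take α = 0.05, β = 0.10". It arrives at 62 patients, raised to 74 (37 per arm) for 20% missed visits. No ICC, design effect, ward count or ward size appears.

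Under Statistical methods, the LSAS and the secondary scales "will be compared using Repeated Measures ANOVA to analyze the efficacy of PEERS training at different time periods", followed by simple effects. Ward is not in the analysis.

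**The concern.** Allocating wards and then looking for patients inside them is a cluster-randomised design. Patients on one ward share staff, environment and case mix, and the Discussion adds that PEERS patients are trained in small groups. Their outcomes are therefore likely to be correlated. A repeated-measures ANOVA handles correlation between visits of the same patient, not correlation between patients on the same ward. Its standard error for the treatment effect is then too small.

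The aim is to validate efficacy, judged at P < 0.05. Under the planned analysis P values would be too small and confidence intervals too narrow, and chance differences between a few wards could be read as an effect of PEERS. The power statement has the same defect, because it counts patients where the design counts wards.

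**Working it through.** **Inputs from the article.** Variance 243.04, so SD = 15.59. Squared difference 272.25, so δ = 16.5. α = 0.05, power 90%, 62 patients before the dropout allowance.

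**Assumptions, not in the article.** ICC from 0.01 to 0.10; W equal-sized wards in total, half per arm; 62 patients analysed (the plan's 74 less the loss it allows for).

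**Reproducing the plan's figure.** 4(1.645 + 1.282)² × 243.04 / 272.25 ≈ 30.6, so 31 per arm and 62 in total. This match needs a one-sided 5% level and the formula read as per arm. It contains no allowance for clustering.

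**Formulae.**
- Ward size m = 62/W; design effect DE = 1 + (m − 1) × ICC.
- True size of the unadjusted two-sided 5% test = 2 × [1 − Φ(1.96/√DE)].
- Valid ward-level test: SE = 15.59 × √(4 × DE/62), on W − 2 degrees of freedom; power from the noncentral t with noncentrality 16.5/SE.

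**One case in full: 4 wards, ICC 0.05.** m = 15.5; DE = 1 + 14.5 × 0.05 = 1.725. Type I error = 2 × [1 − Φ(1.96/1.313)] = 13.6%. SE = 15.59 × √(4 × 1.725/62) = 5.20; noncentrality = 16.5/5.20 = 3.17; the critical t on 2 df is 4.30; power = 42%.

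**Results for ICC 0.01 / 0.05 / 0.10.**

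| Wards in total | Type I error of the planned test | Power of a valid ward-level test |
|---|---|---|
| 2 | 8.6% / 21.5% / 32.7% | not estimable (0 df) |
| 4 | 6.7% / 13.6% / 21.1% | 55% / 42% / 33% |
| 6 | 6.1% / 10.6% / 15.9% | 84% / 73% / 62% |
| 8 | 5.8% / 9.0% / 13.0% | 92% / 85% / 77% |

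A simulation of 40,000 trials per case, with 30 or 31 patients per arm, gave type I errors of 6.1% to 34.6% for 2, 4 and 6 wards, in line with the formula. With 10 wards, the same formula gives about 90% power at ICC 0.05.

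**Would more patients solve it?** Take 4 wards and ICC 0.05. Multiplying 62 by the design effect gives 62 × 1.725 ≈ 107 patients, and the ward-level test then has about 50% power. Even 10,000 patients in 4 wards give only about 68%. With 6 wards, 91 patients give about 82%. The limit is the number of wards.

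**The case against.** Three objections deserve an answer. Each limits the point, and none removes it.

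**Power is not shown to be missed.** A reader might infer that the trial certainly falls short of 90%. The documents do not support that, because the ICC and ward count are unstated. The 62 also contains slack: the usual two-sided formula needs 2 × (1.96 + 1.282)² × 243.04/272.25 = 18.8, so 19 per arm or 38 in total. With independent patients, 31 per arm would give about 98.6% power. That slack can absorb a small design effect if there are enough wards (92% with 8 wards at ICC 0.01). It does not make up for the few degrees of freedom of 4 or 6 wards. The stated power is therefore unsupported, not disproved.

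**Baseline may remove stable ward differences.** Scores are taken at baseline, week 3 and week 6. If baseline enters the ANOVA, a constant difference between wards cancels from the group-by-time interaction, and the ICC that matters there is that of change, which may differ from that of level. It would be too strong to say that any difference between wards will appear as a PEERS effect. Wards whose patients change differently over time still distort the interaction, and the planned simple effects at each visit remain fully exposed.

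**One ward per arm is only a possibility.** A single hospital and a coin toss may suggest two wards, with treatment and ward wholly confounded. The article does not say so, and the point does not depend on it.

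Nor is this detail that an article leaves to a fuller document. The article states the unit of randomisation, the sample-size calculation and the primary test, and the last two conflict with the first.

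**Conclusion.** The point stands and must be fixed. The mismatch between the unit of randomisation and the unit of both the sample size and the analysis is in the article's own text. That the nominal 5% test is anti-conservative holds for any ICC above 0 in the contrast tested. How far depends on two unstated quantities: over ICC 0.01-0.10 with 62 analysed and equal wards, the error is about 9-33% with 2 wards, 7-21% with 4 and 6-16% with 6. The 90% power is unsupported: valid power is 33-55% with 4 wards and 62-84% with 6, and does not exist with 2. For the group-by-time interaction, these ranges should be read with the ICC of change.

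**What to change.** **Statistical methods.** Replace the ANOVA by a mixed model for weeks 3 and 6, with treatment, visit, treatment-by-visit and baseline LSAS as fixed effects and ward and patient as random effects. Test treatment on about (wards − 2) degrees of freedom. Comparing baseline-adjusted ward means is an acceptable alternative.

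**Official experiment.** State the number of wards and restate the power for that number over ICC 0.01-0.10. Do not simply inflate the number of patients by the design effect, since with few wards this does not restore power.

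**If there is only one ward per arm,** state that PEERS and ward are confounded and present the comparison as exploratory, without a confirmatory P value. Neither a mixed model nor more patients repairs that case.

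**Cost.** A change of wording, a less favourable power figure and wider confidence intervals. The named package, SPSS 25.0, fits mixed models. The only data item needed is each patient's ward, which the allocation already requires.
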